## Remote Follow-Up

For patients receiving follow-up at Years 4 - 9, or for patients that have reached the primary endpoint of the trial, there is the option to complete the remainder of follow up remotely without a visit to the clinic. This can be completed by a combination of a phone call to the patient by the site research nurse, review of the patient notes and the patient having the option to complete bloods locally with a blood card. The changes need to be discussed and agreed with the patient as some patients may prefer to continue to attend the hospital clinic. If remote follow-up is preferable and agreed, the discussion and outcome should be documented in the patient's notes.

All SCOT follow-up assessments still have to be adhered to as follows:

- Patient would have the option to complete bloods locally at hospital or GP (as per schedule of assessments foot note 8).
- Blood card to be sent to the patient (please note bloods are not required post recurrence, and only CEA value is required for Years 6 - 9).
- Blood test results must be signed and dated by a member of the site trial staff and filed in the patient notes for source data verification.
- Questionnaires to be posted to the patient if the patient is participating and willing/appropriate to complete.
- Phone call to the patient for survival status and recurrence symptom information
- Review of the patient hospital notes for HEA information.
- CT scans not required.
- SCOT FU CRF to be completed with the above information as per SCOT patient diary.
- Any concerns picked up from remote FU processes should result in an OPA.
- Site needs a system in place to ensure the long term follow-up is completed by SCOT staff listed on the SCOT delegation log and Staff Contact & Responsibilities Sheet, at the required time points as per SCOT patient diary and SCOT protocol.

## 8.1 Quality of Life Questionnaires

At the outset of the trial sites opted to participate in the collection of quality of life and economic questionnaires (EORTC QLQ-C30 & CR29, GOG-NTX 4 and EQ-5D) at PI randomisation.

The collection of detailed toxicity (adverse reactions), QoL and economic data will only be collected for approximately 700 patients as the sample size required for these comparisons is much smaller (see Section 7.4 for full details regarding collection of adverse reaction data).

### EORTC QLQ-C30 & CR29 and EQ-5D Questionnaires

These questionnaires are only completed in a sub-set of patients (patients randomised prior to 16th February 2011 from sites who opted to participate in this sub-study). For this sub-set of patients, the completion of questionnaires must continue as per the SCOT protocol. Please see the Schedule of Assessments for collection time-points.

In addition, for this sub-set of patients who have a confirmed recurrence, or evidence of new tumour, questionnaires should continue to be completed as per schedule of assessments, providing it is deemed appropriate to ask the patient to do so.

Patients participating in the Quality of Life (QoL) Study should complete the EORTC QLQ-C30 and CR29 (a colorectal module which is under development) (Appendix 6) prior to randomisation (baseline) and on day 1 of each treatment cycle (cycles 2-12). In addition, quality of life will be assessed monthly in the 12 weeks arm for the first 3 months post treatment; and in both arms of the trial at 9 and 12 months on study.

In addition to the disease specific EORTC questionnaires, the generic EQ-5D questionnaire (Appendix 8), used for the economic analysis, will require completion at the same frequency as the QoL, however, the EQ-5D questionnaire will also need to be completed by the patient at each follow up visit until study participation is complete (not to be completed by the 24 week patients at the month 6 visit). The following additional data will also be recorded for the economic analysis:

- Cytotoxic drug use at relapse
- Resource use for treating /managing adverse events
- Costs of managing cancer progression

Resource use data collection will be limited to health service resource use only in the secondary care setting.

#### **GOG Ntx 4 Questionnaire**

Similar to the QoL and EQ-5D questionnaires, these questionnaires are only completed in a sub-set of patients. Neurotoxicity is a particular concern with oxaliplatin and this will be assessed using the GOG Ntx 4 questionnaire (Appendix 7). This will require completion at the same frequency as the EQ-5D questionnaire and completed by the patient at each follow up visit until study participation is complete (not to be completed by the 24 week patients at the month 6 visit).

**Completion of this questionnaire for new patients stopped on 16th February 2011. However due to insufficient data it is now requested that sites who opted into this sub-study restart the completion of the GOG Ntx 4 questionnaire in all new patients randomised to the study.**

## **8.2 Pregnancy**

Patients should agree to use reliable birth control during the time they are receiving chemotherapy and for a year after stopping chemotherapy. If the patient or their partner becomes pregnant either whilst receiving trial chemotherapy or in the first year after stopping trial chemotherapy it must be stressed that they are requested to inform their Investigator immediately. Once informed of a pregnancy, sites must immediately complete and fax a Pregnancy Notification Form to their coordinating trial office. The Pregnancy Notification Form must be updated and faxed again as soon as anything relating to the pregnancy changes such as miscarriage, termination or delivery of the baby.

## **9 STATISTICS AND DATA ANALYSIS**

### **9.1 Sample Size**

The study is designed as a non-inferiority trial aimed at excluding a maximum 2.5% fall in 3-year disease-free survival on the 12 week arm (from 78% on 24 week arm; this corresponds to a hazard ratio of 1.13) with 90% power at the 2.5% 1-sided level of statistical significance. Assuming the study recruits over a period of 5-years with a subsequent minimum follow-up of 2 years this will require 8,600 patients to be recruited (a 1:1 allocation will be used) and 2,750 events (relapses/deaths/new colorectal cancers) to be observed. In order to allow for losses to follow-up the actual number we will aim to recruit is 9,500.

In the MOSAIC trial the 3-year DFS on the FOLFOX arm was 78% as compared to 73% with 5 FU/LV . In order to conclude non-inferiority for the 12 week arm we would wish to be confident that at least half of this benefit was retained.

It is acknowledged that disease-free survival rates in the UK may be less than those observed in the MOSAIC trial (for example 3-year disease free survival in the QUASAR study was 64%); however if this is the case this will only enhance the power of the study by increasing the number of events observed during the study period.

The number required for the toxicity, QoL and health economics comparisons is much smaller and it is proposed to collect this information only at centres who agree to participate in these aspects of the study until the required sample size is attained. A sample size of 700 patients (350 on each arm) will allow us to detect (80% power, 5% 2-sided level of statistical significance) a halving in grade 3/4 toxicity rates from 12% to 6% (12% is the rate at which grade 3/4 paraesthesia occurred in the oxaliplatin arm in the MOSAIC trial; paraesthesia was the most frequent non-haematological grade 3/4 toxicity recorded). This same sample size will allow us to detect small changes in global quality of life (assuming a difference of magnitude 7.5 and a standard deviation of 23) with 95% power at the 1% level of statistical significance (to allow for multiple testing). This number should also allow health economics parameters to be estimated reliably, on the basis of the multivariate approach to analysis.

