### 3.2 Enrolment

Recruitment ended on the 29th November 2013. The trial randomised 6087 patients with fully resected stage III or fully resected high-risk stage II colorectal cancer to receive either 24 or 12 weeks of adjuvant chemotherapy over 5.5 years. The treatment regimen was either oxaliplatin/5FU (OxMdG) or oxaliplatin/capecitabine (XELOX). Each individual participating site was able to select which treatment regimen they wished to use for each individual patient prior to randomisation.

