### **3.4 Duration of study**

The trial was due to close in February 2015, with all patients having a least one year of follow-up (with follow-up ending at the end of November 2014). Following a successful application to the funder (outcome November 2015), all Stage III patients should now be followed up for a minimum of 3 years (for the last stage III patient recruited this means the last follow-up is 30 November 2016) and all Stage II patients should be followed up to the end of November 2017. Prior to the approval for the extension of follow up from the funder, there was an interim request to sites to follow up all Stage II patients as per protocol and for Stage III patients yet to reach the 3 year follow up time point until at least November 2015. The reason for this extension is to observe more relapses and thus improve study power, as the study fell below its original recruitment target.

Registration of patients with Medical Research Information Services (MRIS) at the NHS Information Centre for Health and Social Care will enable survival follow-up beyond the specified 9 year period.

A one off update on patient status will be collected on 30th November 2018. Sites will be asked to complete a form to give the following:

- Survival data on all patients previously known to be alive
- For patients who have no record of relapse, any details of subsequent relapse

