## **9.2 Analytical Plan**

### **9.2.1 Primary efficacy analysis**

The primary analysis of the DFS end-point will be based on the intention-to-treat (ITT) population with a supplementary analysis based on the per-protocol population (PP). The per-protocol population is broadly defined as those patients on the 12 week arm who receive 12 weeks of treatment (but do not exceed that) and those patients on the 24 week arm who receive more than 12 weeks treatment.

The primary analysis technique will be Cox regression which will be used to estimate the study arm effect. A test for interaction will be conducted to assess whether the duration effect depends on choice of regimen or the other clinical factors used in the minimisation. This analysis will be conducted at the end of the minimum follow-up period once the required number of events for disease-free survival have been observed.

The degree of potential bias in the PP analysis will be explored by comparing DFS, reasons for non-compliance and characteristics of the patients excluded from each arm. In the event that the PP and ITT analysis lead to differing conclusions regarding non-inferiority the reasons for this will be examined and an additional analysis conducted adjusting for non-compliance.

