## 12 TRIAL MANAGEMENT AND DATA COLLECTION

### 12.1 Study Organisation

SCOT is an independent Investigator led trial run with a grant provided by the Medical Research Council (MRC) UK and sponsored by Greater Glasgow Health Board (GGHB)/University of Glasgow (GU).

Initially it was estimated that approximately 150 sites would be involved in order to enrol 9500 patients over 5 years. The study initiated in March 2008 with the anticipated completion of enrolment in March 2013, and the end of formal trial follow-up in March 2015. Following recommendation by the TSC and approval by the Sponsor and Funder, the enrolment period of the study was extended until the 29th November 2013. The study closed to recruitment on this date with a final recruitment total of 6144 patients.

The trial is being co-ordinated by two trials units, the CR-UK Clinical Trials Unit, Glasgow (CTU) and the Oncology Clinical Trials Office (OCTO), University of Oxford. Each trials unit is responsible for the management/co-ordination of approximately half of the sites participating in the trial. Sites will be informed which trials unit is responsible for their site (their coordinating trial office).

All pharmacovigilance will be managed by the CR-UK Clinical Trials Unit, Glasgow.

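### Sections 9.1 and 9.2.1 still carry the 8,600-patient design and its event trigger after recruitment closed at 6,087, with no restated power and no fallback if 2,750 events are not reached

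*Protocol*

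**What the plan says.** Protocol section 9.1 describes a non-inferiority design "aimed at excluding a maximum 2.5% fall in 3-year disease-free survival on the 12 week arm". The reference rate for the 24-week arm is 78%, the margin is expressed as a hazard ratio of 1.13, and the planned power is 90% at a one-sided 2.5% level. With five years of accrual and at least two years of further follow-up, "this will require 8,600 patients to be recruited (a 1:1 allocation will be used) and 2,750 events (relapses/deaths/new colorectal cancers) to be observed". The recruitment aim is raised to 9,500 to cover losses. The section adds that UK disease-free survival may be lower than 78%, cites 64% from an earlier study, and notes that this would increase the number of events.

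Section 9.2.1 times the primary analysis at the end of the minimum follow-up period, "once the required number of events for disease-free survival have been observed".

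Other sections describe the trial as it turned out. Section 3.2 states: "The trial randomised 6087 patients with fully resected stage III" or high-risk stage II disease, with recruitment ended on 29 November 2013. Section 3.4 extends follow-up to at least three years for stage III (30 November 2016 for the last such patient) and to the end of November 2017 for stage II. It adds a one-off update on survival and relapse on 30 November 2018. The stated reason is to see more relapses and improve power, "as the study fell below its original recruitment target". Section 12.1 gives a different total: "The study closed to recruitment on this date with a final recruitment total of 6144 patients".

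**The concern.** The protocol holds two descriptions of the trial. Sections 3.2 and 3.4 give the achieved recruitment and the extended follow-up. Sections 9.1 and 9.2.1 keep the planned recruitment, the two-year minimum and the 90% power. Section 3.4 says the extension is meant to restore power, but no section says how many events it should yield or what power results.

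The trigger has the same gap. The minimum follow-up could be the two years in 9.1, the three years for stage III or the stage II date in November 2017, and the 2018 update comes after all of them. The only event number in the document is 2,750. If follow-up ends below that number, the rule as written gives no analysis date.

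In a non-inferiority trial, an inconclusive result is judged against the power the trial had. Readers should be able to find that figure, and the date of the analysis should follow from the text.

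**Working it through.** **Inputs.** From section 9.1: three-year DFS 78% against 75.5% at the margin; one-sided alpha 2.5%; power 90%; 8,600 patients, 9,500 with losses; 2,750 events; accrual five years, minimum follow-up two years. From sections 3.2, 3.4 and 12.1: 6,087 randomised; accrual from March 2008 to 29 November 2013, about 5.7 years; cut-offs three, four and five years after accrual closed (November 2016, 2017 and 2018).

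**1. The plan's own figures.**
- Margin: ln 0.755 / ln 0.78 = 1.1311.
- Events for 90% power: 4 × (1.960 + 1.282)² / (ln HR)² = 2,769 at HR 1.1311 and 2,814 at HR 1.13. The stated 2,750 is within 3%.
- Power with 2,750 events: Φ(√2,750 / 2 × ln 1.1311 − 1.960) = Φ(1.27) = 89.8%.
- Hazard: λ = −ln 0.78 / 3 = 0.0828 per year. With uniform accrual over *a* years and minimum follow-up *f*, the event probability is 1 − [exp(−λf) − exp(−λ(f + a))] / (λa).
- With f = 2 and a = 5 this is 0.306 in the 24-week arm, and 0.338 in a 12-week arm at the margin. So 4,300 × (0.306 + 0.338) = about 2,770 events from 8,600 patients.

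The original design is therefore reproduced. Its event count appears to place the 12-week arm at the margin, since equal arms would give 8,600 × 0.3062 = 2,633.

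**2. What the achieved number gives at 78% DFS.** 6,087 / 8,600 = 71% and 6,087 / 9,500 = 64%. Reaching 2,750 now needs events in 2,750 / 6,087 = 45% of patients, against 2,750 / 8,600 = 32% in the design.

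The same formula is applied with a = 5.7. Loss is either zero or the plan's own allowance, 1 − 8,600 / 9,500 = 9.5%, which leaves 5,510 patients. The 12-week arm is either equal to the 24-week arm or at the margin (the plan's apparent counting convention). Power is Φ(√d / 2 × ln 1.1311 − 1.960) for d events.

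| Cut-off | Equal arms, no loss | At margin, no loss | Equal arms, 9.5% loss | At margin, 9.5% loss | Power range |
|---|---|---|---|---|---|
| Nov 2016 | 2,302 | 2,414 | 2,084 | 2,186 | 80-86% |
| Nov 2017 | 2,603 | 2,724 | 2,356 | 2,466 | 85-90% |
| Nov 2018 | 2,880 | 3,007 | 2,607 | 2,722 | 88-92% |

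For example, with 2,302 events: √2,302 / 2 × 0.1232 − 1.960 = 0.996, and Φ(0.996) = 84%.

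No cell reaches 2,750 at either extended follow-up date, although the most favourable one for November 2017 is only 1% short (2,724 / 2,750 = 0.99). At the 2018 update the count lies on either side of the target.

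**3. The lower DFS in section 9.1.** At 64% (λ = −ln 0.64 / 3 = 0.1488) with equal arms, the event probability by November 2016 is 0.5685. That gives about 3,460 events without loss and 3,132 with 9.5% loss, both above 2,750.

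**4. The two totals.** 6,144 − 6,087 = 57. With 6,144 patients, equal arms and no loss, November 2016 gives 2,324 events and 84.4% power, against 84.0% with 6,087. The difference is under half a point.

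**The case against.** The strongest reply is that nothing here is miscalculated. Section 9.1 is a design calculation conditional on its assumptions, and section 12.1 presents 9,500 as the initial estimate. Power follows events, not patients: if the trigger fires at 2,750 events, the trial has about 90% power with 6,087 patients. Section 3.4 discloses the shortfall and responds in the coherent way, with longer follow-up. All of this stands.

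A reader might infer that the target is unlikely to be met, or that the 90% claim is false. The documents do not support either. The target is borderline to met by the 2018 update at 78% DFS, and already passed by November 2016 at the 64% the protocol mentions. A modest departure also suffices: at 73% DFS with equal arms and 9.5% loss, about 2,784 events are expected by November 2017. Lower event counts can be produced by assuming that the hazard falls after year three, but nothing in the protocol supplies such an assumption.

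A reader might also infer that the analysis date will be steered by interim results. Nothing in the protocol says so, and section 14 keeps the complete monitoring reports confidential to the committee members and the trial statistician. Event-driven timing is itself a legitimate choice, so a purely calendar-based cut-off would be a preference.

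Revised power or cut-off details may be in a statistical analysis plan that is not available here. That would not remove the mismatch: the protocol presents superseded recruitment and follow-up as its current sample-size basis, and its own trigger points to that basis.

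**Conclusion.** The point holds as one of stale text and an incomplete timing rule, and should be fixed. On the protocol's 78% planning rate, the stated 90% power is not delivered when the stage III minimum follow-up ends (about 80-86%). It is approached but not quite reached by November 2017 (85-90%), and is met or nearly met at the November 2018 update (88-92%). The loss of power is moderate. The margin, alpha and method of analysis are unaffected.

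The figures assume constant hazard, uniform accrual and every patient followed to the cut-off. The last assumption is generous for November 2017, because section 3.4 asks only stage II patients to be followed to that date. Using the 5.5-year accrual in section 3.2 lowers the counts by about 1% (6,087 × 0.3735 = 2,273 instead of 2,302 for November 2016). The result depends most on the true DFS, which is why a range is needed rather than a single revised power.

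The disagreement between 6,087 and 6,144 is a minor item. It matters for the definition of the ITT set, not for power.

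**What to change.** - **Section 9.1:** keep the original calculation, labelled as the original design. Add the achieved number randomised, the stage-specific follow-up from section 3.4, the expected DFS events at each cut-off and the resulting power, shown over a range of three-year DFS that includes 78% and 64%.
- **Section 9.2.1:** keep the 2,750-event target. State which minimum follow-up applies, and add a calendar date tied to section 3.4 at which the primary analysis goes ahead if the target has not been reached. Record that this date was chosen without reference to comparative data.
- **Margin and level:** leave the 1.13 margin and the one-sided 2.5% level as they are.
- **Sections 3.2 and 12.1:** reconcile 6,087 with 6,144, explain the 57 patients, and name the ITT denominator.

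The cost is wording only, with no new patients or data. The downside is that the stated power becomes somewhat less favourable than 90% at the earlier cut-offs.

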## **9.2 Analytical Plan**

### **9.2.1 Primary efficacy analysis**

The primary analysis of the DFS end-point will be based on the intention-to-treat (ITT) population with a supplementary analysis based on the per-protocol population (PP). The per-protocol population is broadly defined as those patients on the 12 week arm who receive 12 weeks of treatment (but do not exceed that) and those patients on the 24 week arm who receive more than 12 weeks treatment.

The primary analysis technique will be Cox regression which will be used to estimate the study arm effect. A test for interaction will be conducted to assess whether the duration effect depends on choice of regimen or the other clinical factors used in the minimisation. This analysis will be conducted at the end of the minimum follow-up period once the required number of events for disease-free survival have been observed.

The degree of potential bias in the PP analysis will be explored by comparing DFS, reasons for non-compliance and characteristics of the patients excluded from each arm. In the event that the PP and ITT analysis lead to differing conclusions regarding non-inferiority the reasons for this will be examined and an additional analysis conducted adjusting for non-compliance.

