The latter randomisation approach is statistically the optimal approach, especially in this non-inferiority setting, as it excludes from the treatment comparison in an unbiased way patients who would never receive treatment beyond 12 weeks (for toxicity, early progression etc). Such patients add nothing to the question of comparing 12 weeks of treatment with 24 weeks of treatment and simply reduce the power of the study to detect differences.

This approach has been attempted previously in a non-inferiority study seeking to reduce the length of the treatment in non-small cell lung cancer  and was abandoned when only 4 of the first 17 patients opted for randomisation, the remainder wishing to continue therapy.

Whilst randomisation at 12 weeks is the statistically more robust option, it was thought that this would be more difficult to implement in clinical practice. The uncertainty about the length of treatment may be less appealing to the patient and interfere with their ability to plan their life post treatment. This may have a significant impact on the study's ability to recruit the necessary number of patients in a reasonable time frame.

The Short Course Oncology Therapy (SCOT) trial aims to address a number of the issues outlined above. Firstly, is 12 weeks of adjuvant chemotherapy for colorectal cancer equivalent in terms of efficacy to 24 weeks of treatment? Secondly, are the immediate and long term toxicity and quality of life profiles improved by a shorter course of treatment? Thirdly, what are the implications in terms of cost, both in terms of drug costs and resource utilisation? Finally is it possible to randomise at 12 weeks and still achieve adequate recruitment and compliance to achieve the study objectives.

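### The per-protocol rule removes patients who stop at week 12 from the 24-week arm only, and the compliance-adjusted analysis runs only if per-protocol and ITT conclusions differ

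*Protocol*

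**What the plan says.** Protocol section 9.2.1 makes ITT the primary analysis of disease-free survival (DFS) and PP supplementary. The PP definition opens with "The per-protocol population is broadly defined as" and has two limbs. The limb for the shorter arm is "those patients on the 12 week arm who receive 12 weeks of treatment (but do not exceed that"). The limb for the longer arm is "those patients on the 24 week arm who receive more than 12 weeks treatment". No minimum amount of treatment in weeks 13-24 is given.

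Two safeguards follow. The first applies in all cases: "The degree of potential bias in the PP analysis will be explored by comparing DFS, reasons for non-compliance and characteristics of the patients excluded", taking the two arms separately. The second is conditional: "In the event that the PP and ITT analysis lead to differing conclusions regarding non-inferiority the reasons for this will be examined", with an added analysis that adjusts for non-compliance by the method in reference 31.

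Section 1.1 sets the protocol's own benchmark. It prefers randomisation at week 12 on statistical grounds because that removes, without bias, "patients who would never receive treatment beyond 12 weeks (for toxicity, early progression etc"). Delayed randomisation was dropped in July 2009, so from then on all patients were randomised before treatment.

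**The concern.** In a non-inferiority trial, patients who do not receive the allocated duration pull the ITT hazard ratio towards 1, which favours the new arm. A PP analysis is the usual check, and it helps only if its own selection does not distort the comparison.

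Here the arms are filtered on different events after randomisation. Both require 12 weeks of treatment, but the 24-week arm also requires going on past week 12. Those who complete 12 weeks and can go no further are the group that section 1.1 wanted removed from both arms. The PP rule removes them from one.

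The rule also counts as compliant a 24-week patient who has a single cycle after week 12. That is 5 of 8 XELOX cycles (15 weeks) or 7 of 12 OxMdG cycles (14 weeks). At stake is whether agreement between ITT and PP can be read as reassurance, since agreement also switches off the adjusted analysis.

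**Working it through.** **1. The plan's own figures.** Section 9.1 gives 78% 3-year DFS, a 2.5-point margin, one-sided 2.5% and 90% power.

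- Margin: ln(0.755)/ln(0.78) = 1.131, stated as 1.13.
- Events: 4(1.960 + 1.282)²/(ln HR)² = 2,770 at 1.131 and 2,814 at 1.13. The stated 2,750 is within 3% of both. These figures are not in dispute.

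**2. One-sided selection with no true duration effect.** Let e be the share stopping before week 12, excluded from both PP arms. Sections 1.1 and 3.3.2 give 7% for upfront randomisation. Let s be the share who complete week 12 and would stop there, and r their hazard relative to the others. The documents give neither s nor r.

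The 24-week PP arm has relative hazard 1, so PP HR = [s·r + (1 − e − s)]/(1 − e).

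| s | r = 0.8 | r = 1.0 | r = 1.5 |
|---|---|---|---|
| 5% | 0.99 | 1.00 | 1.03 |
| 10% | 0.98 | 1.00 | 1.05 |
| 25% | 0.95 | 1.00 | 1.13 |

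Example: s = 10%, r = 1.5 gives (0.15 + 0.83)/0.93 = 1.05. The top value, 25%, is 32% (drop-out before delayed randomisation) minus 7%. It is an upper bound, because section 3.3.2 shows that the 32% could include patients for whom one of the two durations was not acceptable. The formula averages hazards at the start and ignores later depletion, so it is approximate.

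**3. Dilution left in the PP set.** Let f be the share of the 24-week PP set that stops soon after week 12, and g the share of the extra benefit they lose. With a true full-contrast HR of 1.13, PP HR = 1.13/(1 + 0.13·f·g). The chance of wrongly concluding non-inferiority uses SE = 2/√2,750 = 0.038. A PP set would have fewer events than that, so the last column is only illustrative.

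| f (g = 1) | PP HR | Chance of false non-inferiority |
|---|---|---|
| 0% | 1.130 | 2.5% |
| 10% | 1.116 | 5.3% |
| 20% | 1.101 | 9.9% |
| 30% | 1.088 | 16.9% |

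With g = 0.5 the chances at 10, 20 and 30% are 3.7, 5.3 and 7.3%.

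**4. Can ITT and PP lean the same way?** Take e = 7%, s = 5%, f = 10%, g = 1 and equal prognosis throughout (assumed apart from the 7%). In ITT, the share of the 24-week arm without extra benefit is 0.07 + 0.05 + 0.10 × 0.88 = 0.208. The ITT HR is 1.13/(1 + 0.13 × 0.208) = 1.100, and the PP HR is 1.116. Both fall below the true 1.13. If both led to non-inferiority, the condition for the adjusted analysis would not be met.

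**The case against.** The strongest reply is that PP is supplementary, is defined only in broad terms, and may be refined in an analysis plan not shown here. That stands as a limit on severity, and the lack of a cycle count is not itself the finding. The asymmetric rule and the conditional trigger, however, are stated in the protocol.

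It is also fair that PP bias is acknowledged and that excluded patients will be compared whether or not the analyses agree. That describes the bias but does not correct it.

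A reader might infer more than the documents support:

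- **That the rule biases against 12 weeks.** This holds only if week-12 stoppers have the worse prognosis. With 0.8 times the hazard the sign reverses.
- **That the 24-week arm carries substantial immortal time.** Both arms must get through 12 weeks. The difference is the start of one more cycle: XELOX cycle 5 (week 12) against cycle 4 (week 9), or OxMdG cycle 7 (week 12) against cycle 6 (week 10). At the planned hazard, 3 weeks holds −ln(0.78)/3 × 3/52 = 0.5% event risk, against about 31% over the study. That shifts the HR by at most about 1.6%.
- **That the PP rule creates the dilution.** The same early stoppers are in ITT. PP only fails to remove them.
- **That permitted delays would drop compliant 12-week patients.** Section 3.3.2, section 5.2 on regimen crossover and footnotes 11-12 to the schedule of assessments tie weeks to cycles, which does not support this.
- **That a high minimum-cycle threshold is the answer.** Requiring 75% of cycles would ask 24-week patients to reach XELOX cycle 6 or OxMdG cycle 9 while 12-week patients need only week 12. That reduces dilution but widens the one-sided selection. The protocol's lower cut is a defensible trade-off on that point.

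**Conclusion.** The point holds in a limited form. The PP rule selects the two arms on different post-randomisation events, contrary to the benchmark in section 1.1, and the adjusted analysis is tied to a trigger that shared dilution need not set off.

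Selection alone could show a true HR of 1.00 as about 0.95-1.13. Dilution alone could show a true 1.13 as about 1.12-1.09 for 10-30% stopping soon after week 12. Only the 7% and the 32% behind the upper bound come from the protocol; the other inputs are assumptions. The net direction cannot be fixed from the document: the two biases oppose each other if week-12 stoppers do worse and add up if they do better.

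The primary ITT analysis and the sample size are untouched. What is weakened is the support that agreement between PP and ITT would appear to give.

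**What to change.** 1. Report the compliance-adjusted estimate (reference 31) in every case, not only when ITT and PP conclusions differ. State in cycles what the adjustment counts as compliance, because reusing the PP cut would leave the dilution in.

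2. Add a supplementary comparison by allocated arm from a common week-12 landmark, in patients who are event-free and completed the first 12 weeks (4 XELOX or 6 OxMdG cycles, or the crossover equivalent). Apply no exposure filter after the landmark, so that the same selection applies to both arms. Use one rule in both arms for patients whose delays carry these cycles past calendar week 12. Report the share of each arm reaching the landmark, since allocation is known from the start and could affect completion.

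3. If a minimum number of cycles is wanted for the 24-week arm, keep it as a separate sensitivity analysis and state that it increases one-sided selection.

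The cost is wording and modest extra analysis. Treatment forms are already completed at each cycle, so no new data should be needed. The landmark set will be smaller than the ITT set, and ITT stays primary.
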